**Pre-treatment score**				
**Post-treatment score**				

**Note: osteoporosis symptom grading scale is a measure of pain intensity, using none, mild, moderate, and severe categories with specific scores. Specifically, no pain (0 points); mild pain, without affecting one’s work or life (2 points); moderate pain, affecting one’s work but not life (4 points); severe pain, affecting one’s work and life (6 points)**

#### Indicators for quality of life

Based on quality of life (QOL) and the 36-Item Short Form Survey (SF-36), combined with the specificity of osteoporosis and clinical situations, a self-rating scale in line with Chinese ethnicity was developed (see attached Table 6).

**Table 6 Tab6:** Quality of life questionnaire for patients with osteoporosis

Items	Options			Scores
**I have calf or hand cramps ()**	**Yes (3)**	**No (1)**	**Uncertain (2)**	
**After knowing I had osteoporosis, I felt anxious**	**Yes (3)**	**No (1)**	**Uncertain (2)**	
**I do not know much about osteoporosis**	**Yes (3)**	**No (1)**	**Uncertain (2)**	
**I think that osteoporosis is a very serious illness**	**Yes (3)**	**No (1)**	**Uncertain (2)**	
**I have had fractures**	**Yes (3)**	**No (1)**	**Uncertain (2)**	
**I care about the long time period for the treatment of osteoporosis**	**Yes (3)**	**No (1)**	**Uncertain (2)**	
**I am quite worried about fractures**	**Yes (3)**	**No (1)**	**Uncertain (2)**	
**I think osteoporosis can be cured**	**Yes (3)**	**No (1)**	**Uncertain (2)**	
**I feel that treatment of osteoporosis will increase my financial burden**	**Yes (3)**	**No (1)**	**Uncertain (2)**	
**I may keep thinking about my osteoporosis**	**Yes (3)**	**No (1)**	**Uncertain (2)**	
**I may not do much physical exercises because of osteoporosis**	**Yes (3)**	**No (1)**	**Uncertain (2)**	
**I do the housework a little slower, and a little less than before**	**Yes (3)**	**No (1)**	**Uncertain (2)**	
**I may force me to change my eating habits because of osteoporosis**	**Yes (3)**	**No (1)**	**Uncertain (2)**	
**Travel may be restricted because of my osteoporosis**	**Yes (3)**	**No (1)**	**Uncertain (2)**	
**I may have fewer appointments with my relatives, friends, and children**	**Yes (3)**	**No (1)**	**Uncertain (2)**	
**I think osteoporosis can have an impact on my life**	**Yes (3)**	**No (1)**	**Uncertain (2)**	
**My family may take extra care of me because I have osteoporosis**	**Yes (3)**	**No (1)**	**Uncertain (2)**	
**I think I am in poor health**	**Yes (3)**	**No (1)**	**Uncertain (2)**	
**After knowing I have osteoporosis, I feel I am old**	**Yes (3)**	**No (1)**	**Uncertain (2)**	
**It takes a lot of effort to bend my waist to do things**	**Yes (3)**	**No (1)**	**Uncertain (2)**	
**I often feel pains all over the body**	**Yes (3)**	**No (1)**	**Uncertain (2)**	
**I may get upset because of pains**	**Yes (3)**	**No (1)**	**Uncertain (2)**	
**I seem to have a kyphosis**	**Yes (3)**	**No (1)**	**Uncertain (2)**	
**I am aware that I am getting shorter**	**Yes (3)**	**No (1)**	**Uncertain (2)**	
**I am afraid to go out alone or stay home alone.**	**Yes (3)**	**No (1)**	**Uncertain (2)**	
**The pain caused by osteoporosis interferes with my sleep**	**Yes (3)**	**No (1)**	**Uncertain (2)**	
**Sometimes I have a loose tooth or a removed tooth**	**Yes (3)**	**No (1)**	**Uncertain (2)**	
**I have tinnitus or hearing loss**	**Yes (3)**	**No (1)**	**Uncertain (2)**	
**I have memory loss**	**Yes (3)**	**No (1)**	**Uncertain (2)**	
**I have hyperostosis, herniated disks, or spinal deformities**	**Yes (3)**	**No (1)**	**Uncertain (2)**	
**Pre-treatment score**	**Post-treatment score**			

**Note: the scale is answered by the patient without the physician being involved. The total score of 54 points or less is defined as a normal quality of life, > 54–70 points as decreased quality of life, 71–80 points as the quality of life decreases obviously, and > 80 points as a serious decline in quality of life**

### Blood testing

Sex hormones. Fasting blood samples will be draw every month before and after treatment by the nurse. Chemiluminescence immunoassay (CLIA) will be used to determine serum sex-hormone levels include estradiol (E2), FSH (Model: Berne, Switzerland, ELECSYS2011).Antioxidant index. Before and after intervention, a 5-ml venous blood sample will be obtained under non-fasting conditions. Samples will be frozen at − 70 °C. Advanced oxidation protein products (AOPP), and total antioxidant capacity (TAC) (with 2,2-diphenyl-1-picrylhydrazyl (DPPH) oxidation) will be measured using the following methods: Walwadkar [18], Kataaha et al. [19], Girbal et al. [20], Kitajima [21] and Janaszewska et al. [22].Bone metabolism index. Fasting venous blood will be collected before treatment, one course of treatment and at the end of treatment, respectively. The enzyme-linked immunosorbent assay (ELISA) (biocell enzyme standard instrument) will be used to determine bone gla protein (BGP) and bone alkaline phosphatase (BALP) before and after treatmentPathway signaling proteins. Western blot will be used to detect the expression of β-catenin, FoxO3a and PPARγ2 protein in bone tissue (Multiskan spectrum, Shanghai, China, ThermoScientific, USA).Follow-up is at 6 months after the completion of the treatment. Follow-up will be performed by telephone to ask if the participants have sustained any new fracture or have experienced recurrence of pain.

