### Sample size and blinding

According to the preliminary research [15], we hypothesize that the effective rate after OA is 77.8% and the effective rate after SA is 50%. The equation that we used for this was *α* = 0.05, *β* = 0.20 and we determined that a sample size of 42 patients in each group would be sufficient to detect the statistical difference between the two groups, allowing for a 20% withdrawal rate. We will plan to enroll a total of 104 participants with 52 participants in each group. According to the random number sequence generated by computer, the patients will be randomly divided into either the OA group or the SA group in a 1:1 ratio.

The participants, outcome assessors, study monitors, data managers, and statisticians will be blinded to treatment allocation. If possible, the study participants will be advised to avoid discussing the investigational treatments with other participants. Blinding will be maintained until the 104 participants have completed the study. The success of double-blinding will be assessed at the final visit. Due to the special nature of acupuncture, acupuncturists cannot be blinded to the treatment. The database will then be locked. An emergency code for each individual has been provided to the study researchers and will be disclosed only if it must be known whether a patient is receiving acupuncture treatment or SA in order to manage a serious adverse event.

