### Outcome measures

Outcomes will be collected at baseline, the middle of treatment, after treatment, and follow-up 6 months after the completion of the treatment. The overview of the outcome measurement at the different time points is shown in Table 3.

**Table 3 Tab3:** Overview of study visits

		Study period						
		Enrollment	Allocation	Post allocation			Close out	Follow-up
	Time point (month)	− 1	0	1	2	3		6
Preparation	Enrollment							
	Informed consent	√						
	Eligibility screen	√						
	Allocation		√					
Intervention	OA			√	√	√		
	SA			√	√	√		
Assessment	Liver function Kidney function	√						
	T; BP; P; R	√		√	√	√		
	BMD	√						√
	E2; FSH	√						
	BGP; BALP	√						
	TAC; AOPP	√						
	FoxO3a; β-catenin PPARγ	√						
	VAS	√		√	√	√		√
	TCM syndrome	√			√			
	QOL	√			√			
	Adverse events						√	
	Data analysis						√	
	Fracture rate							√

*T* body temperature, *BP* blood pressure, *P* pulse rate, *R* respiration rate, *OA*, *SA*, *QOL* quality of life, *TCM* traditional Chinese Medicine, *VAS* visual analog scale, *PPAR*, *E2*, *TAC*, *AOPP*, *BGP*, *BALP*, *BMD*, *FSH*

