### Secondary outcomes

#### Pain score

The pain score will be assessed for the lower back. A visual analogue scale (VAS) will be used to measure each group before and after treatment (see attached Table 4).

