**Table 4 Tab4:**
[figure not shown]
Visual analog scale (VAS)

Note: the visual analog scale is a line 10 cm long with a scale of 0–10, in which 0 denotes no pain and 10 denotes the worst pain. Patients are asked to mark their pains on the line, and the examiner scores the VAS by measuring the distance in centimeters (0 to 10) from 0 to the mark

The TCM syndrome scores will be recorded by the same professor once a week to adjust the acupuncture and herbal treatment [17] and evaluate the improvement of the patients’ TCM syndromes (see attached Table 5).

**Table 5 Tab5:** Osteoporosis symptom grading scale (points)

Symptoms	None (0 points)	Mild (2 points)	Moderate (4 points)	Severe (6 points)
**Low-back pain**	**None**	**1–3°**	**4–6°**	**7–9°**
**Soreness and wea kness of waist and knees**	**None**	**After overwalking, I feel a little sore in my waist and knees**	**Somewhere in between**	**Soreness and wea kness of waist and knees continue to occur, and I do not want to stand and****walk**
**Lower limb pain**	**None**	**1–3°**	**4–6°**	**7–9°**
**Impotence and weakness in the lower limbs**	**None**	**After walking(≥ 1 km) I may have sore lower limbs****occasionally**	**After walking** **(300 m–1 km) I may feel weak and sore in my lower limbs**	**After standing and walking (< 300 m) My legs may immediately feel tired**
**Difficulty in walking**	**None**	**It is inconvenient for me to walk occasionally, and I do not feel discomfort walking less than 100 m**	**It is difficult for me to walk even for a short distance (10–100 m)**	**It is difficult for me to stand and walk. And I cannot walk for more than 10 m**
**Dizziness**	**None**	**I get dizzy occasionally, but dizziness does not affect my daily life**	**I get dizzy sometimes, and dizziness would get worse when I am tired, which affects my daily life**	**I get dizzy when I move, and sometimes even fall down, which seriously affects my daily life**

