## Discussion

Acupuncture therapy is a major component of TCM and is increasingly widely used because it is non-invasive and has fewer side effects [23–25]. Drugs for PMOP exists but have some side effects [8], and their long-term effects are unsatisfactory. Some clinical studies have reported the effect of acupuncture on patients with osteoporosis. A recent meta-analysis reported that the quality of evidence was generally low and most studies had small sample sizes (ranging from 30 to 100); therefore, the evidence for the use of acupuncture in postmenopausal women with osteoporosis is not conclusive, and more high-quality, large-sample, multi-center, and well-designed randomized controlled trials should be conducted to provide a reliable basis for further confirmation of the exact efficacy of acupuncture for PMOP [26]. Compared with previous studies, we combined the TCM therapy with a scientific and rigorous experimental design to explore the effects of OA on women with PMOP. The selection of acupoints and herbs is based on the syndrome differentiation in order to adequately demonstrate the dialectical treatment of TCM.

The evidence for the long-term efficacy of acupuncture in patients with PMOP is not sufficient. This trial will conduct a 6-month follow-up of the patient to observe the long-term efficacy of the OA treatment for PMOP. However, a neurological study [27] showed that although SA and placebo had the same effectiveness as manual acupuncture in terms of reduction of symptoms and objective physiological outcomes, verum acupuncture was superior to SA in improving both peripheral and brain neuro-physiological outcomes.

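### Table 3 schedules VAS and BMD at a month-6 follow-up, but the text describes a later telephone call asking about recurrence of pain; mode and date conflict, and recurrence is not a sound randomised measure of long-term pain

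*Protocol article*

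**What the plan says.** The protocol article describes follow-up in several places.

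- **Outcome measures, text:** "Outcomes will be collected at baseline, the middle of treatment, after treatment, and follow-up 6 months after the completion of the treatment".
- **Outcome measures, Table 3:** the follow-up column is labelled month 6. VAS, BMD and fracture rate are ticked in it. VAS is also ticked at enrolment and at months 1, 2 and 3.
- **Pain score:** "A visual analogue scale (VAS) will be used to measure each group before and after treatment". Follow-up is not named here.
- **Note to Table 4:** the VAS is a 10 cm line. "Patients are asked to mark their pains on the line, and the examiner scores the VAS by measuring the distance in centimeters".
- **Blood testing, last item:** "Follow-up is at 6 months after the completion of the treatment". The mode and content come next: "Follow-up will be performed by telephone to ask if the participants have sustained any new fracture or have experienced recurrence of pain".
- **Discussion:** "This trial will conduct a 6-month follow-up of the patient to observe the long-term efficacy of the OA treatment for PMOP".

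The article describes no postal, verbal or electronic form of the VAS and no clinic visit at follow-up.

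**The concern.** Two things look wrong.

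First, the schedule and the text describe different follow-ups. One includes a scale that needs paper and a ruler and a scan that needs a machine. The other is a phone call with two questions. Sites that follow the text would collect neither VAS nor BMD at that point. Sites that follow the table would need a visit that the text does not provide for, possibly at another date.

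Second, if the call is what happens, the only pain information is whether pain has come back. That is a different quantity from pain intensity, and it depends on response to treatment after randomisation. A woman whose pain never eased has nothing to recur.

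At stake is the long-term pain comparison, which is part of the long-term efficacy that the Discussion expects from this follow-up.

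**Working it through.** **Mode.** Table 3 asks for VAS and BMD at follow-up. The note to Table 4 requires the patient to mark a line and the examiner to measure it. The Primary outcome section measures BMD by DXA. Neither can be done in the call described under Blood testing. Either a visit is intended and the telephone sentence is incomplete, or both ticks are wrong.

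**Date.** The numbered columns of Table 3 run −1, 0, 1, 2, 3 and then 6, with allocation at 0 and treatment through month 3. Blood testing and the Outcome measures text both put follow-up 6 months after treatment ends: 3 + 6 = month 9. On the table's own time scale, the label and the text differ by 3 months.

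**What recurrence measures.** The plan gives no recurrence or pain-relief figure, so there is nothing of its own to reproduce. The illustration uses these inputs:

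- R, the share of women whose pain eased: 0.778 for OA and 0.50 for SA. These are the effective rates in Sample size and blinding. Reading them as pain relief is an assumption; the article does not define them that way.
- r, the recurrence risk among women relieved: assumed equal in both arms, varied from 10% to 50%.
- All women start in pain and all answer the call (assumption). There are 52 per arm.

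Counted over all randomised women:

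- recurrence = R × r
- in pain at follow-up = 1 − R × (1 − r)

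At r = 0.30:

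- Recurrence, OA: 0.778 × 0.30 = 23.3%; SA: 0.50 × 0.30 = 15.0%. That is about 12 v 8 women of 52, and OA looks 8.3 points worse.
- In pain, OA: 1 − 0.778 × 0.70 = 45.5%; SA: 1 − 0.50 × 0.70 = 65.0%. OA is 19.5 points better.

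| r (both arms) | Recurrence OA v SA | In pain OA v SA |
|---|---|---|
| 10% | 7.8% v 5.0% | 30.0% v 55.0% |
| 20% | 15.6% v 10.0% | 37.8% v 60.0% |
| 30% | 23.3% v 15.0% | 45.5% v 65.0% |
| 40% | 31.1% v 20.0% | 53.3% v 70.0% |
| 50% | 38.9% v 25.0% | 61.1% v 75.0% |

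In each arm, recurrence minus in-pain equals R × r − 1 + R × (1 − r) = R − 1. The arm difference on recurrence is therefore shifted against OA by 0.778 − 0.50 = 27.8 points relative to the arm difference on pain, whatever the two recurrence risks are. OA would look better on recurrence only if its risk were below 0.50/0.778 = 0.64 times that of SA.

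Counted among relieved women only, equal risk gives 30% v 30%, with no shift in a fixed direction. The comparison is then between about 40 women (0.778 × 52) and 26 (0.50 × 52) selected by their response, so randomisation no longer protects it. It also shows no difference where 45.5% v 65.0% are in pain.

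**The case against.** The strongest reply is that the BMD tick points to an in-person visit. If there is one, the VAS can be taken there and nothing is lost. A reader might infer from the telephone sentence that the follow-up VAS is impossible, but the documents do not settle which passage governs. What stands is that they conflict. The month-6 label could also be loose wording for 6 months after treatment; the other columns count from allocation, so it needs correcting or explaining either way.

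A reader might also infer that the recurrence question necessarily counts against the arm that relieves more pain. The article does not support that. It sets no denominator, does not list recurrence among its outcomes and gives no analysis for it. The shift arises only if recurrence is counted over all women, and even then a low enough risk in OA would offset it. The relief rates and the equal recurrence risk are assumptions, so the percentages show the mechanism and are not estimates for this trial.

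The article is a condensed account, and a telephone script or a definition of recurrence may sit in the full protocol. Their absence is not held against it. The objection to recurrence does not need them: of the two natural denominators, one is shifted by the difference in relief and the other is not a randomised comparison.

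**Conclusion.** The conflict is in the text and needs no assumption: Table 3 and the Blood testing section disagree on how follow-up is done and, on the table's scale, by 3 months on when. The further point is conditional. If the call stands as described, recurrence of pain is not a sound randomised measure of long-term efficacy. Under the stated assumptions, recurrence over all women would show OA 2.8 to 13.9 points worse for common risks of 10% to 50%, while OA is 25.0 to 13.9 points better on pain present.

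This should be corrected, but its reach is limited to the post-treatment follow-up. A reader might infer that the main result is compromised. It is not: the BMD comparison before and after treatment, as the Primary outcome section describes it, and the VAS at months 1-3 do not depend on the call.

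**What to change.** State one follow-up mode and one date, counted from allocation, and make the VAS and BMD ticks in Table 3 agree with them. Removing the VAS tick alone would leave the BMD tick and the date in conflict with the text. As reproduced, Table 3 shows BMD only at enrolment and follow-up, so any change to that tick should keep the end-of-treatment scan in the schedule.

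- **If a visit is intended:** say so where follow-up is described, and take the VAS there in every randomised woman.
- **If telephone is intended:** replace the recurrence question with current low-back pain on a verbal 0-10 scale, asked of every randomised woman whatever her earlier response. Ask the same item beside the VAS at the remaining earlier visits, so that a change of method is not mixed with a change in pain. Compare arms on the verbal score at follow-up, adjusted for baseline pain.

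In either case, do not report recurrence as a randomised efficacy comparison.

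The telephone option costs one extra question at visits already planned, a changed call script and edits to Table 3. The visit option costs the visit itself, which the table already implies. The small downside of the telephone option is that recruitment had begun, so women already enrolled lack a baseline verbal score; their baseline VAS can serve as the covariate.

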### Quality control

In order to ensure the quality of the research, all researchers must attend all training courses and pass the training examinations. They must master all the details of the procedures before they can carry them out. For example, they must master the use of randomization and fill out a case report form (CRF). Acupuncturists should undergo strict and systematic training. The assessor should know how to collect and input data accurately and completely.

To ensure trial quality, clinical monitors designated by the principal investigator will periodically verify all process details.

### Data management

Researchers who have read and understood the standard operating procedures will obtain written consent and collect and manage the study data from the participants, who will be given ongoing encouragement to complete the study. They are telephoned in advanced of each visit and the importance of taking the investigational treatments at the correct times is reinforced. If a participant needs to be withdrawn from the study, the scheduled tests are still performed at the final study visit if the participant is agreeable. If a follow-up investigation is required, researchers will contact the participant by telephone as necessary. After the end of the trial, data entry will be by double entry, and matching will be conducted after inconsistent data has been reviewed. When the data is matched, a data clarification form will be completed and validated.

### Data analysis

The analysis data set will consist of an intention-to-treat data set, a per-protocol (PP) data set, and a safety data set. The intention-to-treat data set will include all subjects assigned to each group. The PP data set will include only participants who adhered to the study protocol and completed the clinical study. The minimum compliance rate for participants taking the acupuncture treatments in the PP data set is 80%. The safety data set will include any participants who were randomly assigned to, and received, at least 1.5 months of the acupuncture treatments. The intention-to-treat analysis will be the primary analysis and will be compared with the PP analysis in a sensitivity analysis. The last-observation-carried-forward method will be used to manage missing data.

All collected data results were compiled using the SPSS 21.0 statistical software package, and collated, checked and statistically analyzed. The comparison between the data groups was performed by using a *χ*^2^ test, and the measurement data was consistent with the normal distribution and the homogeneity of the variance. The mean ± standard deviation ($$\overline{\mathrm{x}}\pm \mathrm{S}$$) indicates that the rank-sum test is used for comparison between grade data sets that do not satisfy the normal distribution and the homogeneity of the variance. *P* < 0.05 was significant for the difference. The variance analysis will be performed for the difference between the two groups and within the group. We will perform a regression analysis to examine the causal relationship between the E2, TAC and β-catenin, and the primary outcome. The statisticians who are independent of the research team will conduct the data analysis.

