### Interventions

Both the OA and SA groups will receive acupuncture sessions for a total of 3 months. All the patients will receive herbal medicine twice a day for 3 months. The same physician (the Professor of Acupuncture in Yunnan Provincial Hospital and Traditional Chinese Medicine, who has 20 years of work experience) will slightly adjust the formula each week depending on the changes of the symptoms, pulse, and tongue coating of the patients (main herbal formula components are shown in Table 1). During the trial, patients will be classified by pattern differentiation: (1) spleen-kidney *Yang* deficiency will be given Yougui Pill; (2) liver-kidney *Yin* deficiency will be given Zuogui Pill; and (3) kidney deficiency and blood stasis will be given Bushen Huoxue decoction. Participants will be given all the herbs from the same hospital and the physician will instruct them how to decoct.

**Table 1 Tab1:** Main herbal formula selection

Pattern	Formula	Composition
Spleen-kidney *Yang* deficiency	Yougui Pill	radix rehmanniae preparata, cortex cinnamomi, cornu cervi degelatinatum, rhizoma dioscoreae, fructus corni, fructus lycii, radix angelicae sinensis, cortex eucommiae, semen cuscutae, radix morindae officinalis, rhizoma drynaria, rhizoma sparganii
Spleen-kidney *Yin* deficiency	Zuogui Pill	radix rehmanniae preparata, rhizoma dioscoreae, fructus lycii, fructus corni, radix achyranthis bidentatae, deerhorn glue, deerhorn glue, radix morindae officinalis
Kidney deficiency and blood stasis	Bushen Huoxue decoction	radix rehmanniae preparata, semen cuscutae, cortex eucommiae, fructus lycii, radix angelicae sinensis, fructus corni, cistanches herba, commiphora myrrha, radix angelicae biseratae, radix angelicae sinensis

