According to the OA and moxibustion [15], and taking opinions from Chinese acupuncture experts, the essential acupuncture points selected are as follows: BL11 (Dazhu), BL23 (Shenshu) and ST36 (Zusanli). The additional individualized acupuncture points will be chosen by the practitioners according to the patterns of identification: (1) kidney *Yang* deficiency will have added DU04 (Mingmen), GB34 (Guanyuan); (2) spleen-kidney *Yang* deficiency will have added DU04 (Mingmen), GB34 (Guanyuan); (2) liver-kidney *Yin* deficiency will have added SP06 (Sanyinjiao), LU11 (Taixi); (3) kidney deficiency and blood stasis will have added SP06 (Sanyinjiao), BL17 (Geshu) (Table 2). A placebo device [16] will be applied in both groups for better implementation of blinding. The schematic diagram of the acupuncture treatment is shown in Fig. 2.The acupuncture treatment in both groups will take 30 min per session, twice per week. Three months is the duration of a course of treatment, for a total of one course .

**Table 2 Tab2:** Acupuncture point selection

Point	Location
BL11 (Dazhu)	In the spinal region, under the spinous process of the 1st thoracic vertebra, 1.5 cun lateral to the posterior midline
BL23 (Shenshu)	1.5 cun beside the spinous process of the 2nd lumbar vertebra
ST36 (Zusanli)	At the anterior aspect of the leg 3 cun inferior to ST35 (Dubi) on the line connecting ST35 (Dubi) to ST41 (Jiexi)
DU04 (Mingmen)	Between the spinous processes of the 2nd and 3rd lumbar vertebrae
GB34 (Guanyuan)	On the lower abdomen at the anterior midline, 3 cun below the umbilicus
SP06 (Sanyinjiao)	On the tibial aspect of the leg posterior to the medial border of the tibia, 3 cun superior to the prominence of the medial malleolus
LU11 (Taixi)	On the posteromedial aspect of the ankle in the depression between the prominence of the medial malleolus and the calcaneal tendon
BL17 (Geshu)	Under the spinous process of the 7th thoracic spine on the back, 1.5 cun lateral to the midline

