### Adverse events

Safety will be assessed by body temperature, pulse rate and character, respiratory rate, blood pressure, renal function test, and liver function test. These indicators are detected during the period of screening and after 12-week treatment. We will monitor adverse events for each treatment during the trial, including hematomas, skin burns, skin infections and acute pain. Any adverse events or reactions that are thought to be causally associated with the intervention will be recorded, managed, and reported to the study coordinators. Serious adverse reactions will be reported to the Ethical Committee.

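### The safety data set admits only participants with at least 1.5 months of acupuncture, so anyone who stops before then is left out of the safety analysis

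*Protocol article*

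**What the plan says.** The Data analysis section sets up three analysis populations. The safety one carries an exposure threshold: "The safety data set will include any participants who were randomly assigned to, and received, at least 1.5 months of the acupuncture treatments". The intention-to-treat one carries none: "The intention-to-treat data set will include all subjects assigned to each group".

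The Interventions section fixes the length and frequency of treatment: "Both the OA and SA groups will receive acupuncture sessions for a total of 3 months", and "The acupuncture treatment in both groups will take 30 min per session, twice per week".

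The Adverse events section has events monitored at every treatment and names burns, hematomas, infections and acute pain among them. It then adds: "Any adverse events or reactions that are thought to be causally associated with the intervention will be recorded". Serious reactions go to the ethics committee. The Data management section keeps the final-visit tests for withdrawn participants who agree to them.

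On numbers, the Sample size and blinding section says "We will plan to enroll a total of 104 participants with 52 participants in each group", after "allowing for a 20% withdrawal rate". Safety is a declared aim: both the Introduction and the Discussion list it beside efficacy and mechanism.

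**The concern.** A safety population normally starts at first exposure, because intolerance is one of the main reasons for stopping. Here, entry depends on something that happens after randomisation and that harm itself can prevent. A participant who stops in week 2 with a skin burn is in neither the numerator nor the denominator of the adverse event rate. Those who remain have, by construction, kept going for six weeks or so.

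The rule also works against the plan's own data collection. Events are looked for from the first session, yet those of early stoppers have no place in the population named for analysing them. The safety set can therefore be smaller than the intention-to-treat set used for efficacy.

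At stake is whether the trial can support a statement about the safety of overall adjustment acupuncture (OA). The primary analysis of bone mineral density is not affected.

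**Working it through.** The article states no size for the safety set, so there is no figure to reproduce. The check has three steps: how much exposure the threshold demands, how many people it could remove, and what that does to an adverse event rate.

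**Inputs**
- Threshold for the safety set: 1.5 months (Data analysis).
- Planned course: 3 months, two sessions a week (Interventions). The Adverse events section refers to 12 weeks of treatment; three calendar months are about 13 weeks.
- Randomised: 104, that is 52 per group (Sample size and blinding).
- Planned withdrawal: 20%, for any reason and at any time (same section).
- Share of withdrawals before 1.5 months, *f*: not given. It is an assumption, run from 0 to 1.

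**Step 1: exposure required.** 1.5 / 3 = 50% of the course. At two sessions a week the full course is 2 × 12 = 24 to 2 × 13 = 26 sessions, so the threshold is about 12 to 13 sessions.

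**Step 2: participants removed.** Planned withdrawals are 0.20 × 104 = 20.8, about 21. Assume that those who withdraw have each had at least one session. Then the number removed is 104 × 0.20 × *f*, and the safety set is 104 minus that.

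| *f* (assumed) | Removed | Safety set |
|---|---|---|
| 0 | 0 | 104 |
| 0.25 | 5.2 | 98.8 |
| 0.5 | 10.4 | 93.6 |
| 0.75 | 15.6 | 88.4 |
| 1 | 20.8 | 83.2 |

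**Step 3: effect on a rate.** Within an arm, let *d* be the share of treated participants removed, *p_e* the event rate among them and *p_s* the rate among those who stay. The rate in everyone treated is *d·p_e* + (1 − *d*)·*p_s*; the rate reported under the rule is *p_s*. The understatement is the difference, *d*·(*p_e* − *p_s*). It is zero if nobody leaves early, or if early leavers have events no more often than the rest. It is positive whenever harm prompts some of the early stopping. If an arm loses exactly the planned 20%, all before 1.5 months, *d* = 0.20. The ceiling is then 0.20 × (1 − 0) = 20 percentage points, reached only if every early leaver and nobody else has an event. The documents give no value for *p_e* or *p_s*, so nothing narrower can be derived.

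**Text check.** No other section defines a second safety population or brings back those who stop before 1.5 months. Table 3 marks adverse events only at close-out; I have taken the Adverse events text, with monitoring at every treatment, as describing collection.

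**The case against.** The best defence is that little information is lost. Events are monitored at each treatment, serious reactions are reported, and withdrawn participants can still have their final tests. Safety is not the primary outcome, and the intention-to-treat analysis is untouched. All of this is true. It shows that the fault lies in the analysis population and not in data collection, which also makes it easy to repair. It does not make the definition sound.

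Several stronger readings are tempting, and the article does not support them.

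- *Everyone who stops early is excluded.* Those who stop between 1.5 and 3 months stay in the set. Only stopping before 1.5 months matters.
- *Harm is hidden more in the OA arm.* This is plausible, since OA uses penetrating needles and stronger stimulation. It is not shown: the sham arm also receives cupping, at lower negative pressure, and no event or discontinuation rates by arm are given. The rule applies equally to both arms.
- *Unblinded acupuncturists decide which events count.* The Sample size and blinding section does say "Due to the special nature of acupuncture, acupuncturists cannot be blinded to the treatment", but nothing says that they judge causality. The article does not name who does.
- *Only events believed to be related are recorded.* The sentence in the Adverse events section can be read that way. It can also be read as a reporting route for related events, after a sentence that already provides for monitoring at each treatment. The wording is unclear, so this point is secondary.
- *The rule would turn a substantial event rate into zero.* One could suppose that 6 of 52 OA participants stop early with an event and none of the other 46 has one, giving 6/52 = 11.5% in truth and 0/46 as reported. That is a single extreme case with no basis in the documents. The planned 20% covers all causes, including withdrawal for prohibited medication.

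**Conclusion.** The definition is wrong as written and should be changed. Following it exactly removes from the safety analysis every participant who stops before half the course, including those who stop because of harm. The loss is between 0 and about 21 of 104 treated participants. This assumes that withdrawal matches the planned 20% and that each person withdrawing has had at least one session. The position within that range depends on the unknown timing of withdrawal, and zero is possible.

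The direction of the error is downward whenever harm contributes to early stopping. Its size, and whether it differs between arms, cannot be settled from the article. Even an equal loss in both arms would understate the absolute rates. Confidence is high for the population definition and lower for the recording sentence, which has two readings.

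**What to change.** In the Data analysis section, define the safety set as all randomised participants who received at least one real or sham acupuncture session, analysed by the treatment actually received, and state that adverse events will be reported by arm in that set. If the 1.5-month exposure group is of interest, keep it as a descriptive table only.

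As a secondary change, reword the sentence in the Adverse events section so that all adverse events are recorded in both arms, with relatedness as a separate field, and say who makes that assessment.

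The cost is small: a sentence or two in each section and slightly more recording on the existing case report form. Treatment, visits, sample size and the primary analysis do not change. The change should be made before the database is locked and the allocation revealed.
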